### Data analysis

Study data will be analyzed following an intent-to-treat (ITT) approach. The ITT-population consists of all patients who provide informed consent and receive at least one treatment session.
What is the persistence rate of DSM-5 moderate to severe SUD from adolescence to young adulthood among youth in the 2 and 4 years following entry in addiction treatment?

Persistent moderate to severe SUD is defined as meeting the criteria of lifetime moderate to severe SUD for alcohol, cannabis, cocaine or amphetamines – collapsed across substances – at baseline, as well as meeting the criteria of past-year moderate to severe SUD at both the 2 year and 4 year follow-up. According to DSM-5, moderate to severe SUD is defined as meeting four or more of the 11 SUD-criteria. In case of missing follow-up data we will conduct sensitivity analyses, using multiple imputation methods based on post-baseline treatment, end-of-treatment and follow-up data that we do have available of a participant. We will also conduct a ‘worst-case’ scenario analysis, in which those not reached at both the two- and four-year follow-up are considered as youth with persistent SUD. Notably, for youth without past-year SUD at the 2 year follow-up and a missing 4 year follow-up (and vice versa), our primary outcome variable is available: they are – by definition – youth with non-persistent SUD.
(2)What is the prognostic value of a general population-based set of predictors of persistent SUD from adolescence to young adulthood for predicting persistent DSM-5 moderate to severe SUD among youth in addiction treatment?

We will use existing data from the Tracking Adolescents’ Individual Lives Survey (TRAILS) study to investigate the rate of persistent substance dependence (DSM-IV) and its predictors from adolescence to young adulthood in the general population. TRAILS is a prospective cohort study (*N* = 2230) into the development of mental health from preadolescence (age 11 years) to adulthood (up to age 26 years) in the Dutch general population with five biennial or triennial follow-up waves [58]. Candidate-predictors stem from the areas of: demographic background; substance use and SUD; non-SUD mental disorders; family history; life events; and social functioning (see first six domains in Table 1). Logistic regression will be used to investigate the relation of these predictors with the outcome variable, persistent substance dependence, following the two-step procedure suggested by Hosmer and Lemeshow (2000) [59]. Only variables which are significantly associated with the outcome variable in the first, univariate, step will be entered as candidates into the multivariate (backward) logistic regression model in the second step. Next, we will evaluate the accuracy of the set of combined adolescent risk factors found to predict persistent substance dependence in the TRAILS cohort for predicting persistent DSM-5 moderate to severe SUD among youth in addiction treatment, in terms of sensitivity, specificity, and positive and negative predictive value.
(3)Can we optimize the accuracy of predicting persistent DSM-5 moderate to severe SUD among youth in addiction treatment by extending or modifying the general population-based set of predictors with baseline indicators from our addiction treatment sample?

This question will be addressed (a) by building a new prediction model based upon the same potential predictor variables as used in the TRAILS analysis above, and supplement these with potential predictor variables assessed at baseline in our addiction treatment sample (Table 1), and (b) by comparing the accuracy of this treatment-based prediction model with the TRAILS-population-based prediction model.
(4)Which longitudinal treatment outcome trajectories can be identified from adolescence to young adulthood pertaining to substance use and SUD, comorbid mental health problems, and social functioning among youth in addiction treatment?

Concerning the fourth study question, we will use the total count of DSM-5 SUD-symptoms derived from the MATE-Y, and the sum score on the DASS-21 (mental health problems) and WHODAS 2.0 (social functioning), assessed at baseline and at two- and four-years follow-up (Table 1). To describe the longitudinal course of SUD, mental health problems and social functioning we will employ latent growth curve modeling [60].
(5)Which treatment interventions – in terms of type, intensity and duration – are associated with favorable or unfavorable long-term outcomes, in terms of substance use and SUD, mental health problems and social functioning, for which youth in addiction treatment?

The fifth study question will be answered in two successive steps. First, we will determine which treatment interventions are associated with a favorable treatment outcome, using the same two-step logistic regression procedure as described for study question 3. Next, we will determine whether the youth-related potential predictors for persistent SUD (see study question 3) moderate the favorable or unfavorable long-term outcomes of the different treatment interventions. To determine which treatment interventions are associated with a favorable long-term – two- and four-years – outcome, we will categorize the treatment received along the following dimensions: type of treatment; intensity; duration; type of termination (see section ‘Treatment’ above).

All study questions will be analyzed using the statistical software packages of SPSS version 25, R, and Mplus, where appropriate.

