**Methods/design:**

In a naturalistic, multi-center prospective cohort design, we will include youths (*n* = 420), who consecutively enter addiction treatment at ten participating organizations in the Netherlands. Inclusion is prestratified by treatment organization, to ensure a nationally representative sample. Eligible youths are 16 to 22 years old and seek help for a primary DSM-5 cannabis, alcohol, cocaine or amphetamine use disorder. Assessments focus on lifetime and current substance use and SUD, non-SUD mental disorders, family history, life events, social functioning, treatment history, quality of life, chronic stress indicators (hair cortisol) and neuropsychological tests (computerized executive function tasks) and are conducted at baseline, end of treatment, and 2 and 4 years post-baseline. Baseline data and treatment data (type, intensity, duration) will be used to predict outcome – persistence of or desistance from SUD.

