**Fig. 1 Fig1:**
[figure not shown]
Flowchart of the Youth in Transition study

Inclusion criteria are: age 16 to 22 years; primary SUD pertains to cannabis, alcohol, cocaine or amphetamines; willingness to participate in the study (oral and written informed consent). Exclusion criteria are: referral for diagnostic evaluation only; insufficient comprehension of basic Dutch language. The ten participating organizations include specialized addiction treatments and integrated mental health and addiction treatments, with treatment covered by the health insurance system. Recruitment of study participants takes place at 41 treatment locations situated throughout the Netherlands.

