### Power considerations

Using a sampling fraction of 10% to obtain a representative sample from the total target population (*N* = 4169; see ‘Participants and setting’ above), we aim to include 420 youth in our study. Concerning our first study question, we assume a 30% persistence rate of moderate to severe SUD in our study sample [20, 21, 52]. With precision at 5% [53], a minimum sample size of *N* = 300 would be sufficient to estimate the assumed 30% persistence rate with a 95% level of confidence [54].

However, for our prediction analyses of persistent SUD (study questions 2, 3 and 5) we need a larger sample size than N = 300 to allow a sufficiently large number of predictor variables to be included in the logistic regression models. To avoid overfit of a logistic regression model, authors recommend a minimum of 10 events (i.e., 10 patients with persistent SUD) for each predictor variable [55–57]. Hence, given the assumed 30% persistence rate, and *N* = 420, a maximum of 12 predictor variables could be included in the multivariate logistic regression analysis.

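### Youth who never reached moderate to severe SUD by baseline stay in the persistence denominator but cannot be events, and those who worsen are coded with the desisters

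*Protocol article*

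**What the plan says.** - **Entry.** The inclusion criteria (Participants and setting) ask that "primary SUD pertains to cannabis, alcohol, cocaine or amphetamines". The abstract says that eligible youth "seek help for a primary DSM-5 cannabis, alcohol, cocaine or amphetamine use disorder". Neither sets a minimum number of criteria.
- **Analysis set.** Data analysis states: "The ITT-population consists of all patients who provide informed consent and receive at least one treatment session". Baseline severity plays no part.
- **Outcome.** Under study question 1, persistent SUD is "defined as meeting the criteria of lifetime moderate to severe SUD for alcohol, cannabis, cocaine or amphetamines" at baseline, together with "meeting the criteria of past-year moderate to severe SUD at both the 2 year and 4 year follow-up". The threshold is explicit: "moderate to severe SUD is defined as meeting four or more of the 11 SUD-criteria". The abstract describes the outcome as "persistence of or desistance from SUD", which leaves no category for worsening.
- **Planning rate.** Power considerations says "we assume a 30% persistence rate of moderate to severe SUD in our study sample" and derives a limit of 12 predictors from all 420 participants.
- **Missing data.** The worst-case analysis codes as persistent every youth missed at both follow-ups. No baseline condition is attached.

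**The concern.** The set being analysed is wider than the set that can have the outcome. Three things follow.

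1. **Study question 1.** The reported proportion is the rate among youth at risk of persistence multiplied by the share of the sample at risk. It moves with case mix at entry as well as with the course of the disorder.
2. **Study questions 2 and 3.** Substance use and SUD is one of the candidate predictor domains, and baseline SUD is in Table 1. Youth without the lifetime condition contribute no events by construction, so baseline severity predicts the outcome partly by definition. These structural non-events can raise specificity and negative predictive value, which are among the accuracy measures the protocol names.
3. **Meaning of the non-event.** A youth who goes from fewer than four criteria to moderate to severe SUD at both follow-ups is pooled with youth who recovered. The Background section describes the earlier treatment studies as showing persistence or deterioration in roughly 15 to 30%. The protocol's own definition places this kind of deterioration on the other side.

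**Working it through.** **Reproducing the plan's figures.** Inputs from Power considerations and Participants and setting: p = 0.30, precision d = 0.05, 95% confidence, target population 4169, N = 420, 10 events per predictor.

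- n0 = 1.96² × 0.30 × 0.70 / 0.05² = 322.7. With finite population correction, 322.7 / (1 + 321.7/4169) = 299.6, which is the stated 300.
- Events: 0.30 × 420 = 126. Then 126/10 = 12.6, which gives the stated 12. This result takes all 420 as the denominator, so the plan does apply the rate to everyone enrolled.

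**Who is outside the at-risk set.** The baseline condition is lifetime and is collapsed across the four substances. The affected youth are those who had never met four criteria by baseline. Call their share m. The documents give no value for m, so 5%, 10% and 20% below are assumptions. Complete follow-up is taken throughout, as in the plan's own event count.

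**Formulas**
- Full-set rate = (1 − m) × at-risk rate.
- At-risk rate = full-set rate / (1 − m).
- Half-width = 1.96 × √(p(1 − p)/n), with n = 420 × (1 − m) and no finite population correction.

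| m | Youth outside | n at risk | Full-set rate if 30% is the at-risk rate | Events | Predictors at 10 events each | At-risk rate if 30% is the full-set rate | Half-width at p = 0.30 |
|---|---|---|---|---|---|---|---|
| 5% | 21 | 399 | 28.5% | 119.7 | 11 | 31.6% | 4.5 points |
| 10% | 42 | 378 | 27.0% | 113.4 | 11 | 33.3% | 4.6 points |
| 20% | 84 | 336 | 24.0% | 100.8 | 10 | 37.5% | 4.9 points |

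- With all 420 the half-width is 1.96 × √(0.21/420) = 4.4 points.
- On the first reading (30% is the at-risk rate), the shift is 0.30 × m. It exceeds 5 points only when m > 0.05/0.30, about 17%. Twelve predictors need 120 events, so 0.30 × (420 − k) ≥ 120 allows at most k = 20 youth outside the at-risk set, or 20/420 = 4.8%.
- On the second reading (30% is the full-set rate, as the protocol words it), all 126 events already lie in the at-risk set. Restriction then loses no events and the limit stays at 12. The half-widths at 31.6%, 33.3% and 37.5% are 4.6, 4.8 and 5.2 points.

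**Worseners among the non-events** (first reading; the worsening shares are also assumptions)
- m = 10%, 20% of them worsening: 42 × 0.20 = 8.4 of 420 − 113.4 = 306.6, or 2.7%.
- m = 20%, 30% of them worsening: 84 × 0.30 = 25.2 of 420 − 100.8 = 319.2, or 7.9%.

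**Worst-case rule against the definition.** The protocol notes that a youth without past-year SUD at one follow-up is non-persistent by definition even if the other follow-up is missing. The same logic makes a youth without the baseline condition non-persistent whatever follow-up shows. Yet the worst-case rule, as written, would code that youth persistent if both follow-ups are missed.

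**The case against.** The strongest reply is that the protocol asks for a rate among youth entering treatment and states its 30% for the study sample. A rate per entrant is a coherent quantity for a study that aims at a representative treatment cohort. That stands: the full-set proportion is not meaningless, and no discrepancy from the protocol's own 30% has been shown. It does not remove the difficulty in the prediction models, where the non-events mix recovery, absence of risk and deterioration.

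Four stronger readings may tempt a reader. The document does not support them.

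- **Every youth with mild SUD at entry is locked out.** The condition is lifetime, so a youth currently below four criteria who once met four can still be persistent. The affected group is narrower, and in a treatment-seeking sample it may be small.
- **The persistence rate is biased by several points.** That takes 30% as the at-risk rate and also needs a value for m, which the document does not give.
- **Worsening is lost, or modelled as a good outcome throughout.** Study question 4 follows the DSM-5 symptom count with growth curves and would show it. For study question 5 the protocol does not define a favourable outcome, so the problem reaches that question only where the persistence outcome is reused.
- **The lifetime condition is itself an error.** It does let relapse after remission at entry count as persistence. But it is an explicit choice, and it fits the chronic-intermittent course described in the Background section.

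It may also be said that an article condenses, and that denominators belong in the analysis plan. The article does not state a separate denominator for study question 1. It does fix the analysis set for the study data and the outcome definition, and its predictor limit uses all 420. The mismatch lies between statements that are already made.

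**Conclusion.** The point holds in limited form. Eligibility and the analysis set include youth who had never met four criteria by baseline. The primary definition makes them non-events whatever happens later. Those with moderate to severe SUD at both follow-ups are coded with the desisters in study question 1 and in the models of study questions 2 and 3. The worst-case analysis can code the same youth the opposite way.

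The size is unknown because m is not given. On the assumption that 30% is the at-risk rate, the loss is 1.5, 3.0 or 6.0 points for m of 5%, 10% or 20%. If 30% is the full-set rate, as worded, the rate among youth at risk is 1.6, 3.3 or 7.5 points higher than the reported figure. The correction is worth making because it is cheap and settles what a non-event means; a large error has not been demonstrated.

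**What to change.** 1. For study question 1, for the persistence models in study questions 2 and 3, and for study question 5 where it uses the persistence outcome, restrict the sample to youth who meet the stated baseline condition (lifetime moderate to severe SUD).
2. Apply the same condition in the worst-case analysis.
3. Report the remaining youth separately, including how many progress to moderate to severe SUD. The rate per treatment entrant can still be shown as a labelled supplementary figure.
4. Recompute the predictor limit from the events in the restricted set.
5. A past-year baseline definition may be added as a sensitivity analysis. It need not replace the lifetime one.

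**Cost.** This is wording in the analysis plan. Lifetime and past-year diagnoses are already collected at baseline, so no new data are needed. The interval widens slightly: at an assumed m of 10% and a rate of 30%, from 4.4 to 4.6 points with n = 378. It would pass 5 points only in the less favourable combinations, such as m = 20% with an at-risk rate of 37.5% (5.2 points). The predictor limit may fall from 12 to 11 or 10 if 30% proves to be the at-risk rate.

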### Participants and setting

Based on national treatment registration data [23], a total of 5769 youth up to age 22 years applied for addiction treatment in the Netherlands in 2015. From these, the far majority (*N* = 5151; 89%) were 16 to 22 years old, and most sought help for a primary cannabis- (53%), alcohol- (17%) or stimulant- (11%, cocaine or amphetamine) related problem. Hence, 81% (*N* = 4169) of total treatment demand among youth aged 16–22 years concerns cannabis, alcohol, cocaine and/or amphetamines, with other substances (e.g., opiates, ecstasy, GHB, and benzodiazepines) each representing less than 2% of treatment demand. Limiting our inclusion to youth aged 16–22 years, with the primary substances mentioned above, and using a sampling fraction of 10%, 420 youth will be included in our study (see Fig. 1).

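### Youths who never reached moderate to severe SUD by baseline cannot be 'persistent' but stay in the denominator, so the persistence rate is diluted and the non-persistent class is mixed

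*Protocol article*

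**What the plan says.** All references are to the protocol article.

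- **Entry** (Participants and setting, inclusion criteria): "primary SUD pertains to cannabis, alcohol, cocaine or amphetamines". No severity threshold is set.
- **Analysed set** (Data analysis): "The ITT-population consists of all patients who provide informed consent and receive at least one treatment session". The article names no narrower set for questions 1, 2, 3 or 5.
- **Outcome** (Data analysis, question 1): persistence is "defined as meeting the criteria of lifetime moderate to severe SUD for alcohol, cannabis, cocaine or amphetamines", pooled over substances, at baseline, plus moderate to severe SUD in the past year at each of the two follow-ups. The cut-off is four of the 11 DSM-5 criteria.
- **Predictors** (Data analysis, question 2): "Candidate-predictors stem from the areas of: demographic background; substance use and SUD", with four further domains. Accuracy is judged by sensitivity, specificity and predictive values.
- **Size** (Power considerations): "we aim to include 420 youth in our study", and "we assume a 30% persistence rate of moderate to severe SUD in our study sample".
- **Missing data** (Data analysis, question 1): the worst-case analysis counts everyone missed at both follow-ups as persistent, without reference to baseline severity.

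**The concern.** The outcome has a baseline condition that neither the entry criteria nor the analysed set contains. A youth with fewer than four criteria by baseline, in any period of life and for every substance assessed, is fixed as a non-event before follow-up starts. With six criteria at both 2 and 4 years, that youth is still non-persistent, the same class as a youth who recovered.

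Two results are affected. First, the rate for question 1 mixes two quantities: how often moderate to severe SUD persists, and how many entrants had it to begin with. It is read as the former. Second, in questions 2 and 3 any predictor that reflects lifetime baseline severity gains accuracy from the definition alone, because it identifies youths who could not be events. The comparison of the TRAILS-based model with the treatment-based model can partly reflect this.

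**Working it through.** **The plan's own figures.** Inputs from Participants and setting and Power considerations: rate 0.30, half-width 0.05, 95% confidence, target population 4169, sample 420, 10 events per predictor.

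- Without a finite-population correction: 1.96² × 0.30 × 0.70 / 0.05² = 322.7, so 323.
- With the correction: 322.7 / (1 + 321.7/4169) = 299.6, so 300. This matches the stated minimum.
- Events: 420 × 0.30 = 126, and 126/10 = 12.6, so 12 predictors. This matches.

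**Effect on the rate.** Let m be the share of the analysed set never at moderate to severe level by baseline. The documents do not give it, so 2% to 20% is assumed. These youths contribute no events, so

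rate over all = rate among those at risk × (1 − m).

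This can be read from either end:

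| Assumed m | At-risk youths, 420(1 − m) | At-risk rate 30%: rate over all | Rate over all 30%: at-risk rate |
|---|---|---|---|
| 2% | 412 | 29.4% | 30.6% |
| 5% | 399 | 28.5% | 31.6% |
| 10% | 378 | 27.0% | 33.3% |
| 20% | 336 | 24.0% | 37.5% |

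The third column is 0.30(1 − m); the fourth is 0.30/(1 − m). In the third column the shift is 0.30m, or 0.6, 1.5, 3.0 and 6.0 points. It exceeds the plan's 5-point precision only when m is above 0.05/0.30 = 16.7%.

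**Accuracy gained by definition.** As an illustration, take a yes/no flag for lifetime moderate to severe SUD at baseline that has no relation to outcome among those at risk (at-risk rate 30%). Every event carries the flag, so sensitivity and negative predictive value are 100%. Specificity is m / (1 − 0.30(1 − m)), and AUC is (1 + specificity)/2:

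- m = 2%: specificity 0.02/0.706 = 3%, AUC 0.51
- m = 5%: 0.05/0.715 = 7%, AUC 0.54
- m = 10%: 0.10/0.730 = 14%, AUC 0.57
- m = 20%: 0.20/0.760 = 26%, AUC 0.63

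The link is exact only for lifetime status. For past-year severity or days of use it is a weaker, induced association.

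**Worst-case rule.** The article notes that a youth without SUD at one follow-up is non-persistent by definition, even if the other follow-up is missing. The same logic applies to a youth below the cut-off by baseline, yet the worst-case rule counts that youth as persistent if both follow-ups are missing.

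**The case against.** The strongest reply is that a whole-cohort denominator is a legitimate choice. The research question concerns youth in addiction treatment, and the absolute risk of chronic moderate to severe SUD among all entrants is useful. The TRAILS rate and predictors are also described for the general population, with no stated restriction to those already dependent, so restricting only the treatment cohort could break the parallel. This stands as a reason to keep the whole-cohort analysis as a secondary one. It does not make the whole-cohort figure a persistence rate. Nor does it justify the mixed non-event class: an absolute-risk outcome would count youths who progress to moderate to severe SUD at both follow-ups, and this definition excludes them.

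The share may also be small. The baseline window is lifetime, pooled over four substances, in youths seeking treatment. At an assumed 2% the effect is 0.6 points. This limits the size of the problem without removing it. Worsening is not wholly hidden either, because question 4 models the symptom count at every assessment.

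An article may leave detail to a fuller document. Here, however, the analysed set and the outcome definition are both stated, and it is their combination that fails.

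Three stronger readings are tempting and are not supported:

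- *The limit of 12 predictors is too high.* Youths below the cut-off contribute no events, so removing them changes no event count. The 30% is stated for the whole study sample, so 126 events and 12 predictors stand.
- *A severity indicator would give a diverging logistic fit and be dropped by a Wald screen.* The article names a predictor domain, not a binary severity indicator, and does not say which univariate test is used.
- *Question 5 counts progression as favourable.* The article does not define a favourable outcome, and question 5 also covers mental health and social functioning.

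**Conclusion.** The point holds in limited form. As written, youths who never reached moderate to severe SUD by baseline are in the denominator, cannot be events, and share a class with youths who recovered. The direction is certain: if any such youths are enrolled, the reported figure is below the rate among those who had the condition, by the factor (1 − m). The size is not known. It is 0.6 to 3.0 points for an assumed m of 2% to 10%, inside the plan's 5-point precision, and 6.0 points at 20%, outside it. These figures take 30% as the rate among those at risk. If 30% is the whole-sample rate, as Power considerations states, the at-risk rate is 30.6% to 37.5% over the same range of m.

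The effect on prediction accuracy is real but partial. It is small at m of 10% or less, and applies fully only to predictors that encode lifetime baseline severity. The sample-size figures in Power considerations reproduce and need no correction on this account.

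**What to change.** In Data analysis:

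1. Make the primary persistence rate, and the persistence models fitted or evaluated in the treatment sample, conditional on lifetime moderate to severe SUD at baseline. This covers questions 2 and 3, and question 5 where persistent SUD is the outcome.
2. Report the number of youths below that cut-off, and their rate of moderate to severe SUD at 2 and 4 years, separately.
3. Keep the whole-cohort rate and model as a secondary analysis for comparison with TRAILS.
4. Keep all youths in the question 4 growth models.
5. Apply the same baseline condition to the worst-case rule.

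The baseline DSM-5 criteria are already collected with the MATE-Y (Assessments), so the cost is wording and a slightly smaller analysed set. At an assumed m of 5%, 10% or 20%, 399, 378 or 336 youths remain before any loss to follow-up, all above the stated minimum of 300. The half-widths are 1.96 × √(0.21/n) = 4.5, 4.6 and 4.9 points without a finite-population correction, against 4.4 for all 420. The margin over 300 would run out only at m = 1 − 300/420 = 28.6%.

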## Study objectives

In this study, we will investigate the rate of persistent SUD and its predictors longitudinally from adolescence to young adulthood in a representative treatment sample of youth with DSM-5 SUD from the start of their addiction treatment to 2 and 4 years following treatment-entry. In addition to SUD, we will investigate the course of comorbid mental disorders and social functioning, and their relation with SUD over time.

Our primary study questions are:
What is the persistence rate of DSM-5 moderate to severe SUD from adolescence to young adulthood among youth in the two and four years following entry in addiction treatment?What is the prognostic value of a general population-based set of predictors of persistent SUD – based on the Dutch Tracking Adolescents’ Individual Lives Survey (TRAILS) study – from adolescence to young adulthood for predicting persistent DSM-5 moderate to severe SUD among youth in addiction treatment?Can we optimize the accuracy of predicting persistent DSM-5 moderate to severe SUD among youth in addiction treatment by extending or modifying the general population-based set of predictors with baseline indicators from our addiction treatment sample?Which longitudinal treatment outcome trajectories can be identified from adolescence to young adulthood pertaining to substance use and SUD, comorbid mental health problems, and social functioning among youth in addiction treatment?Which treatment interventions – in terms of type, intensity and duration – are associated with favorable or unfavorable long-term outcomes, in terms of substance use and SUD, mental health problems and social functioning, for which youth in addiction treatment?

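### Question 3 builds its treatment-sample model by a univariate gate and backward elimination, which overfits at about 126 events, and its comparison does not isolate the gain from the added indicators

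*Protocol article*

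**What the plan says.** Question 3 (Study objectives) asks whether prediction of persistent SUD can be improved "by extending or modifying the general population-based set of predictors with baseline indicators from our addiction treatment sample". Under Data analysis it is to be answered "by building a new prediction model based upon the same potential predictor variables as used in the TRAILS analysis above", supplemented with other baseline variables from Table 1, and by comparing the accuracy of that model with the TRAILS-based one.

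The selection rule appears under question 2, for the TRAILS data: "Only variables which are significantly associated with the outcome variable in the first, univariate, step will be entered as candidates" for a backward multivariable logistic model. The question 3 paragraph states no rule of its own, but question 5 is to be analysed "using the same two-step logistic regression procedure as described for study question 3". The article therefore treats the two-step rule as the question 3 method. It gives no significance level for either step.

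Power considerations says "we aim to include 420 youth in our study", "we assume a 30% persistence rate of moderate to severe SUD in our study sample", "authors recommend a minimum of 10 events" per predictor, and concludes that "a maximum of 12 predictor variables could be included in the multivariate logistic regression analysis".

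**The concern.** Screening by single-variable p-values and then eliminating backward is a noisy way to build a prediction model when events are few. Weak but real predictors fail the gate by chance. Those that survive tend to be the ones whose estimates came out too large, and no shrinkage follows. The limit of 12 predictors applies to the multivariable model, whereas selection runs over the whole candidate pool, so the limit does not guard against this.

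A second point concerns what the comparison measures. Neither the TRAILS predictors nor their weights are carried into the new model. A difference in accuracy therefore mixes three things: re-estimated weights, chance re-selection, and the information in the added treatment-sample indicators.

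Question 3 is one of the five primary study questions. At stake are how well predicted risks would hold in new patients, and whether the answer speaks to the value of the added indicators.

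**Working it through.** **The plan's own figure.** Events = 420 × 0.30 = 126. At 10 events per predictor, 126 / 10 = 12.6, so 12. The stated limit reproduces.

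**Size of the candidate pool.** The article gives no count. The Assessments section lists ten non-SUD disorders, three DASS-21 dimensions and four SURPS scales. If each is a candidate, that is 10 + 3 + 4 = 17, already above 12, before substance use, family history, life events, social functioning, the computerized tasks and the hair measures.

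**Chance that a real predictor passes the gate** (two-sided p < 0.05 assumed). For a standardised continuous predictor, SE ≈ 1/√(N·p·(1−p)) = 1/√(420 × 0.3 × 0.7) = 1/√88.2 = 0.1065, and power ≈ Φ(ln OR/SE − 1.96). For OR 1.3: 0.2624/0.1065 = 2.464, and Φ(0.504) = 69%. Likewise OR 1.2 gives 40%, OR 1.4 gives 88% and OR 1.5 gives 97%. For a binary predictor with 20% / 50% prevalence, OR 1.5 gives 36% / 47% and OR 2.0 gives 78% / 90%. With an assumed 20% loss (N = 336), continuous OR 1.3 falls to 60%. Strong predictors pass; weak or binary ones often do not.

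**Whole procedure, by simulation.** Effect sizes, candidate numbers, correlations and p < 0.05 at both steps are assumptions, because the article gives none. N = 420 with 30% events; AUC is measured in new subjects.

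- Set A: 400 runs, 30 candidates, 8 TRAILS and 4 extra predictors real at OR 1.3 per SD. TRAILS weights are ideal or carry random error (SD on the log-odds scale). The extension adds 12 extra candidates without a penalty.
- Set B: 100 runs, 20 shared candidates (8 real) and 10 extra (3 real) at OR 1.35. The TRAILS model is itself selected at N = 2230 with 9% events. The 9% is borrowed from the birth-cohort rate in the Background.

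| Setting | TRAILS | Two-step rebuild | TRAILS score extended | Rebuild worse than TRAILS |
|---|---|---|---|---|
| A, ideal TRAILS weights | 0.679 | 0.651 | 0.704 | 90% |
| A, weight error SD 0.15 | 0.658 | 0.649 | 0.683 | 64% |
| A, weight error SD 0.25 | 0.636 | 0.653 | 0.665 | 33% |
| B, same effects, independent | 0.695 | 0.674 | 0.717 | 80% |
| B, same effects, correlation 0.2 | 0.815 | 0.808 | 0.828 | 70% |
| B, effects differ SD 0.15, correlation 0.2 | 0.809 | 0.815 | 0.821 | 32% |
| B, effects differ SD 0.30, correlation 0.2 | 0.789 | 0.822 | 0.802 | not recorded |

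In set A with ideal weights the rule kept 4.1 of 8 real TRAILS predictors and 2.1 of 4 real extras, plus about 0.6 null variables. All eight TRAILS predictors survived in about 1% of runs. With six TRAILS predictors at OR 1.5, 87% were kept and all six survived in 42% of runs. Loosening the gate to 0.25 helped only a little: 4.9 of 8 and 2.4 of 4 kept.

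**Calibration.** The two-step model's slope in new subjects was 0.68–0.84 across eight settings in the set B layout, and 0.68–0.86 across seven settings of a further set (60 runs each). One layout with 10 real predictors among 30 gave 0.64 at OR 1.3 and 0.79 at OR 1.5. A slope below 1 means coefficients too extreme.

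**Alternative.** In those seven settings a cross-validated lasso on the whole list had slopes of 0.92–1.07. Its AUC ran from 0.019 better to 0.005 worse than the two-step model.

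**The case against.** Four counter-arguments carry weight.

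*The loss of discrimination depends on assumptions.* It is clear when many predictors are weak and both cohorts share the same effects. Shared effects are not assured: TRAILS is a general-population cohort with a DSM-IV dependence outcome, and this study follows treated youth with a DSM-5 outcome. When effects differ enough, the rebuild overtakes the TRAILS model, as the table shows. With few strong predictors (4 + 2 real, OR 1.7) the two-step model reached 0.776, against 0.757 for ridge and 0.774 for the extension. This stands, so a reader may not infer that the plan will generally predict worse.

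*No single replacement wins everywhere.* An extension with fixed TRAILS weights lost to the plan when effects differed at SD 0.25 (0.705 against 0.735), and pure ridge lost at OR 1.7 (0.755 against 0.772). Adding 12 null extras without a penalty also cost accuracy (0.673 against 0.698). This stands and shapes the fix.

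*A reader might infer that the plan will miss a real gain.* That can happen when accuracy is judged in new patients or after internal validation. If accuracy is read in the development data, the error runs the other way. In set A the rebuild then looked better than TRAILS in 96–99.5% of runs with real extras, and in 64–97% with none real. The article does not say which reading is planned, and that detail may sit in the SAP. Correcting the optimism would make the reported accuracy honest but would leave the same overfitted model in place.

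*A reader might infer that the analysis contradicts its question, or that differing predictor lists will be taken as differences between populations.* The text supports neither. The question allows the set to be modified as well as extended, so re-selection is permitted. The planned comparison is of accuracy; no comparison of predictor lists is described.

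**Conclusion.** The point holds in a limited form. The two-step rule is a stated method for question 3, although it reaches that question through a cross-reference. At about 126 events it gave coefficients that were too extreme in every setting where slope was measured, mostly 0.7 to 0.85.

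The loss in AUC is conditional. It appears when real predictors are many and weak, where about half are dropped and the rebuild can fall below the TRAILS model (0.651 against 0.679 in set A with ideal weights). It disappears when predictors are few and strong or when effects differ greatly between cohorts. Separately, the planned comparison does not isolate the contribution of the added indicators.

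All sizes beyond the 126 events and the limit of 12 rest on assumed effects, candidate numbers and significance levels, and some settings had only 60 or 100 runs. Missing outcomes would reduce the events further. This is a weak method with a cheap improvement, not an error that invalidates question 3.

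**What to change.** For question 3, replace the univariate gate and backward elimination as follows:

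- **Modified model:** a penalised logistic model that can both select and shrink (lasso or elastic net, cross-validated penalty), fitted to the whole candidate list.
- **Extended model, reported beside it:** the recalibrated TRAILS linear predictor plus the treatment-sample baseline indicators under a penalty.
- **Comparison:** both against the recalibrated TRAILS model, using cross-validated or bootstrap-corrected accuracy.

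Neither the fixed-score extension nor pure ridge should be the sole primary model, since each loses to the plan in plausible settings. The two-step model may stay as a descriptive result.

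The cost is a change of wording and a little more analysis. No new data are needed, and R is already named. The final model will list more variables with shrunken coefficients, so it gives a less compact set of risk factors. If predictors turn out few and strong, up to about 0.005 of AUC may be given up.
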